### Blinding

SAVER is an open-label trial. The primary endpoint of the trial consists of objective assessments of lesion size using a clinical photograph, grade of dysplasia and loss of heterozygosity studies. These will all be assessed by blinded assessors.

### Statistical analysis

There will be no formal stopping rules or interim analysis based on patients’ response rate. However, an Independent Safety and Data Monitoring Committee (ISDMC) will meet at regular intervals to review and assess the conduct of the study and the accumulated data. The ISDMC will be able to make appropriate recommendations to the Trial Steering Committee (TSC) on grounds of toxicity and feasibility.

The study will be analysed and reported in line with the Consolidated Standards of Reporting Trials (CONSORT). Statistical analyses will be carried out following the intention to treat principle (ITT), with the exception of toxicity which will be analysed on the basis of the actual treatment received. Missing data are not anticipated to be substantial in the study and therefore the final analysis shall be performed on a complete case basis. However, if more than 10% missing data are observed on the primary outcome, multiple imputation technique by chained equations shall be used.

Continuous variables will be summarised as median and interquartile range and categorical variables will be presented as frequencies of counts with associated percentages. Primary analysis on the primary outcome will be performed using a stratified Mantel Haenszel test and results will be assessed with a one-sided p value of 0.16 as the threshold for statistical significance. The primary efficacy parameter (odds ratio) will also be reported with the one-sided 84% confidence interval. Logistic regression will be used to investigate the relationship of the primary outcome with key prognostic covariates. Analyses of categorical secondary outcome will mirror that of response rate, using stratified Mantel Haenszel test and logistic regression techniques. Time to event data will be compared between arms by stratified log-rank test. Further analyses on survival data shall be carried out using Cox models if, after inspection of Schoenfeld residuals, the proportional hazard assumption is not violated. All secondary analyses will be assessed by the nominal two-sided p value of 0.05 to determine statistical significance.

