### Randomisation

Randomisation will be completed centrally by the LCTC via a password-protected web-based tool called the Treatment Allocation Randomisation System (TARDIS). All patients will be allocated a unique randomisation number. Randomisation must be carried out within 90 days of the research biopsy report and commencement of trial treatment within 30 days of the date of randomisation. Patients will be randomised between VPA (arm A) and observation only (arm B) in the ratio 2:1, with site used as a stratification factor.

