#### Assessment of histology response score

A 9-point scale will be used to obtain the histological score as related to the grade of dysplasia. The histology response score is the original pathology score minus the final pathology score (from the specimen obtained at the end of the 4-month treatment period). See Table 4.

**Table 4 Tab4:** Histological scoring scale

Score	Histological diagnosis
0	Normal with or without hyperkeratosis
1	Atypia with crisply defined clinical margins
2	Mild dysplasia
3	Mild-moderate dysplasia
4	Moderate dysplasia
5	Moderate-severe dysplasia
6	Severe dysplasia
7	Carcinoma in situ
8	Invasive squamous cell carcinoma

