#### Assessment of loss of heterozygosity (LOH) response score

LOH has been identified as a prognostic marker for progression of OED, with lesions displaying LOH at 3p and 9p having a 22-fold increased risk of progression to OSCC [20]. The following 8 loci and associated genes have been selected based on previous evidence of their predictive value in the progression of OED:
3p14 [D3S1007 (VHL), D3S1234 (FHIT)]9p21 [D9S171, D9S1748 (P16/CDKN2A), D9S1751 (P16)]9p22 (IFN-a)17p13 [D17S786 (P53) and TP53]

For each loci, a score of +1 is given if it is positive for LOH and zero if it is negative for LOH. The LOH response score will be the pre-treatment score minus the post-treatment score.

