### Sample size calculation

Sample size calculations are carried out on the principles of a single-stage Jung design for randomised phase II studies based on exact binomial probabilities and allowing for unequal allocation [21]. The primary outcome is the response rate; a rate of 20% is estimated for the control arm with a 20% rate increase in the treatment arm representing the minimal clinically important difference. With a type I error of 0.16 and 82% of power, 100 patients (33 in the observation-only arm and 67 in the treatment arm) will be required in the study. Adjusting for a potential 10% drop-out rate, the final sample size will be of 110 patients (37 in the observation-only arm and 73 in the treatment arm).

The intent of the study will be to recruit the 110 patients required over a period of 32 months, assuming 10 sites recruiting at an average rate of 0.4 patients per site per month.

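### The primary test is valid but omits baseline histology score and LOH count, which cap two of the three components of the response score; adjusting for them would protect against chance imbalance and may add power

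*Protocol article*

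**What the plan says.** The Statistical analysis section of the protocol article fixes the decision rule: "Primary analysis on the primary outcome will be performed using a stratified Mantel Haenszel test". It does not list the strata. On the threshold it adds that "results will be assessed with a one-sided p value of 0.16 as the threshold for statistical significance". The Randomisation section gives 2:1 allocation "with site used as a stratification factor" and names no other factor, so a site-stratified test is an inference, though the obvious one.

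The Statistical analysis section also plans a logistic regression to look at how the primary outcome relates to prognostic covariates. It does not name the covariates and does not give that model the treatment decision.

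Two of the three components of the score are changes from baseline. For dysplasia grade (0 to 8 scale), "The histology response score is the original pathology score minus the final pathology score". For the 8 loci, "The LOH response score will be the pre-treatment score minus the post-treatment score". The third, lesion size, is a relative change coded from -3 to +3. The three are summed, and a total of 1 or more counts as response. The Abstract places baseline tissue collection before randomisation.

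The Sample size calculation uses a "single-stage Jung design for randomised phase II studies based on exact binomial probabilities and allowing for unequal allocation", that is, a comparison without covariates.

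**The concern.** Because histology and LOH are scored as baseline minus follow-up, the largest gain on each equals the baseline value. Table 1 admits mild, moderate and severe dysplasia, which are 2, 4 and 6 on the histology scale, so the possible histology gain runs from 2 to 6 points. A patient with no LOH at baseline can score only 0 or below on LOH; one with five positive loci can gain up to 5. Measurement error in the baseline biopsy adds regression to the mean in both arms. Baseline values should therefore carry some information about who is classed as a responder.

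Neither randomisation nor, on the natural reading, the primary test takes them into account. In a trial of this size, a chance difference between arms in grade or LOH count would then pass straight into the response difference. The Rationale section says the result will inform the decision on a phase III trial, so readers will ask whether baseline differences explain it. Choosing covariates after unblinding would be a weak answer.

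**Working it through.** **Inputs from the protocol.** "With a type I error of 0.16 and 82% of power, 100 patients (33 in the observation-only arm and 67 in the treatment arm"; "a rate of 20% is estimated for the control arm with a 20% rate increase in the treatment arm"; one-sided 0.16; 10 sites; 2:1 allocation. The protocol does not say how strongly baseline grade and LOH predict the 4-month response, so that is assumed over a range.

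**1. The plan's own figure.** Exact enumeration of two binomials, one-sided Fisher test at 0.16, 33 v 67, 20% v 40%: power 80.5%, actual type I error 0.104. An exact rule on the rate difference, with type I error evaluated at 20%, gives 87.7% power and type I error 0.151. The stated 82% lies between these and roughly reproduces.

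**2. Range of the total score.** Maximum = 3 (size) + baseline grade + baseline LOH count.
- Grade 2, no LOH: 3 + 2 + 0 = 5.
- Grade 4, 4 loci: 3 + 4 + 4 = 11.
- Grade 6, 8 loci: 3 + 6 + 8 = 17.

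The caps differ widely, but all lie above the threshold of 1.

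**3. Difference needed for significance** (normal approximation, 20% in both arms): 0.994 × sqrt(0.2 × 0.8 × (1/67 + 1/33)) = 0.994 × 0.4 × 0.2127 = 0.085, or 8.5 points.

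**4. Chance imbalance.** The SD of a standardised baseline difference is sqrt(1/33 + 1/67) = 0.2127.
- P(above 0.2 SD, either direction) = 2 × (1 − Φ(0.2/0.2127)) = 35%.
- P(above 0.3 SD, either direction) = 2 × (1 − Φ(0.3/0.2127)) = 16%.

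These are per factor.

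**5. Effect of a 0.3 SD imbalance.** Shift = 0.3 × sqrt(R²) × sqrt(0.2 × 0.8), with R² the share of variance in response explained by baseline.
- R² 0.04: 0.3 × 0.20 × 0.4 = 0.024, about 2 points.
- R² 0.13: 0.3 × 0.36 × 0.4 = 0.043, about 4 points.

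That is about a quarter to a half of 8.5 points.

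**6. Power at 20% v 40%** (simulation, N = 100, 10 sites, 2:1 blocks within site, one-sided 0.16, 2,500 to 3,000 replicates, Monte Carlo SE about 0.7 points):

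| Assumed R² (AUC) | Site-stratified Mantel-Haenszel | Baseline-adjusted logistic |
|---|---|---|
| 0 (0.50) | 86% | 86% |
| 0.04 (0.64) | 87% | 87% |
| 0.13 (0.74) | 88% | 91% |
| 0.24 (0.82) | 86% | 93% |
| 0.35 (0.87) | 86% | 95% |

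**7. A rough model of this composite.** The distributions of grade and LOH are assumed, with three levels of reading noise: grade SD 0.4, 0.8, 1.2; misread per locus 3%, 8%, 15%.

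| Noise | R² | Control response, grade 2 → 6 | Control response, 0 → 7 loci | Mantel-Haenszel power | Adjusted power |
|---|---|---|---|---|---|
| Low | 0.012 | 17% → 22% | 10% → 26% | 85.6% | 85.6% |
| Middle | 0.034 | 15% → 24% | 7% → 32% | 85.9% | 86.1% |
| High | 0.064 | 13% → 27% | 5% → 39% | 86.3% | 87.8% |

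Type I error was 0.163 to 0.168 for the site-stratified test and 0.162 to 0.174 for the adjusted one. Splitting each site stratum by baseline grade (about 20 strata of 5 patients) lowered power to 82.1% to 84.0%. In these composite runs the adjusted model held grade and LOH count but no site term, and no site effect was simulated, so they do not show what site costs inside the model.

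**The case against.** The strongest reply is that nothing is wrong with the test. It matches the randomisation, the trial was sized for an unadjusted comparison, and the stated power roughly reproduces. Chance imbalance is already part of the variance behind the 8.5-point threshold, and regression to the mean acts on both arms alike. All of this stands: it is a matter of efficiency and robustness.

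Second, the strata are inferred, a covariate regression is already planned, and a separate analysis plan may name its terms. The inference is conceded. But the protocol itself says which analysis is primary, and it uses the regression to describe associations.

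Third, the gain may be negligible. This also stands. A reader might infer from the capped scores that the plan throws power away; the documents do not support that, because the loss depends on a prognostic strength they do not give, and it is near zero in the rough composite model.

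A reader might also infer that the caps keep low-baseline patients from responding. They do not: mild dysplasia without LOH can still total +5 against a threshold of +1.

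Nor should one-standard-error shifts from the two baselines simply be added. Under one assumed set of inputs they are 1.45 × 0.213 × 6.7 = 2.1 points (histology) and 1.9 × 0.213 × 3.8 = 1.5 points (LOH). The sum, 3.6, needs both to fall the same way. If they are independent, the combined figure is sqrt(2.1² + 1.5²) = 2.6 points, about 30% of 8.5.

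Finally, the model has few events to work with: 0.2 × 33 + 0.4 × 67 = 33.4 expected responders. Treatment, two covariates and nine site indicators make 12 terms, under 3 responders per term. That is a fair warning about the form of the model. It also argues against adding baseline lesion area, for which there is no supporting calculation; the size score is a relative change that baseline area does not cap.

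**Conclusion.** The point holds as a worthwhile improvement to a valid plan. Baseline histology score and LOH count are fixed before treatment, bound two of the three components, and are absent from the primary comparison on the natural reading of the protocol. The firmer benefit is protection from chance imbalance: about a 16% chance per factor of exceeding 0.3 SD, with a shift of roughly 2 to 4 points at that imbalance if R² is 0.04 to 0.13. The rough composite model gave R² of only 0.01 to 0.06, so the lower end is the better supported. The power gain is about 0 to 2 points in that model and reaches about 9 (86% to 95%) only if baseline is strongly prognostic (R² 0.35). Every figure that involves R² rests on assumption. The arithmetic of the caps, the imbalance probabilities and the 8.5-point threshold follow from the protocol's definitions and design figures. If the analysis plan already makes an adjusted comparison primary, the point is met.

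**What to change.** Before unblinding, pre-specify the primary treatment comparison as a logistic model with treatment, baseline histology score, baseline LOH count and site, with the treatment term tested at one-sided 0.16. State one fixed rule for handling small sites, chosen without sight of outcome by arm. Before finalising, confirm by simulation that type I error stays near 0.16 with site in the model, since the composite runs above did not include it.

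Report a standardised risk difference with the odds ratio, and say that the odds ratio is conditional on the covariates. Keep the site-stratified Mantel-Haenszel test as the sensitivity analysis. Do not add baseline factors as further Mantel-Haenszel strata, which lowered power in the simulations.

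The cost is wording in the protocol and analysis plan; no new data are needed. There are two small downsides. The adjusted odds ratio is not the same quantity as the Mantel-Haenszel one, and with about 33 expected responders the covariate list must stay short.

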### Ethical considerations

The trial protocol has been reviewed and approved by North West - Haydock Research Ethics Committee and REC reference: 18/NW/0180. The trial has been registered with the MHRA; the ISRCTN number is 12448611.

### Sodium valproate safety profile

Sodium valproate is licensed for use in epilepsy and bipolar disorder. It is also used off-label for depression, neuropathic pain, dementia and migraine. Very common adverse effects, defined as occurring in >10% of patients, include nausea and tremor. Common adverse events (between 1 and 10% of patients) include upper abdominal cramps, transient increase in liver enzymes, weight gain and diarrhoea, transient alopecia, reduced bone density, thrombocytopenia and anaemia. Neurological adverse effects such as fatigue, sedation, confusion and dizziness are also observed commonly. Due to the significant risk of birth defects and developmental disorders in babies born to mothers taking VPA during pregnancy, the MHRA have issued guidance advising: ‘Valproate medicines must no longer be used in women or girls of childbearing potential unless a Pregnancy Prevention Programme is in place’. Women of childbearing potential (WOCBP) will not be recruited to the trial, due to known teratogenic effects of VPA [22]. All women will require a follicular stimulating hormone (FSH) test prior to randomisation, to confirm post-menopausal status. The exception to this is women who have undergone total hysterectomy or bilateral salpingo-oophorectomy.

The SAVER trial will use VPA at 1000 mg/day; this is a low to medium dose, associated with mild or absent toxicities, and is well tolerated [23]. Higher doses, sometimes justified in epilepsy, are associated with weight gain, tremor, drowsiness and cognitive slowing. In the context of premalignant oral conditions, we feel that these would not be justified. The impact of weight gain will be reduced by excluding obese patients (BMI > 30).

#### Potential risks of delay to surgical treatment

Study participants who are listed for surgical excision of OED will have their surgery scheduled at the end of month 4 of the study. This is considered an acceptable timeframe as the progression of OED to invasive cancer is reported to take an average of 4 years from diagnosis [3]. It is also in keeping with common clinical practice at most HNC services in the UK, which prioritise treatment of invasive oral cancer [24].

### Criteria for discontinuing or modifying allocated interventions

Patients may be withdrawn from treatment for any of the following reasons: Development of an OSCC, unacceptable toxicity, any change in the patient’s medical condition that justifies discontinuation of treatment in the clinician’s opinion and pregnancy.

Treatment may be discontinued for any toxicity with a significant impact on quality of life (generally grade 2 or higher; however, persistent grade 1 adverse events (AEs) may also lead to discontinuation). A 50% dose reduction (500 mg/day) may also be considered for persistent grade 1 toxicities rather than withdrawal from the trial. Patients discontinuing due to toxicity will be followed up and assessed as per protocol. Patients discontinuing treatment for any reason will continue to be followed up unless the patient explicitly withdraws consent for follow-up. If the patient explicitly states their wish not to contribute further data to the study, a withdrawal CRF will be completed. Anonymised data collected up to this point can still be used for study purposes.

### Assessment of compliance with study treatment

All patients will have plasma valproate levels measured at 2 months and 4 months; this will confirm that patients in the observation-only arm are not taking sodium valproate and will help to confirm patient compliance in the treatment arm. In addition, patients in the treatment arm will be given a drug diary sheet to be completed each day. Research Nurses will collect the unused tablets and completed diaries and record any circumstances of non-compliance in the patient notes and on the CRF. The returned medication will be sent to the site pharmacy for storage.

### Recruitment

The main feasibility outcome is the recruitment rate. Ten sites have been selected to allow an achievable recruitment rate of 0.4 patients per site per month (approximately 4 patients per month) with a total of 110 patients. Targets for recruitment will be set at 43 and 88 for 12 and 24 months respectively. As a guide, it is proposed that if the study will be recruiting within 80% of the intended rate (at least 34 and 70 for 12 and 24 months, respectively) then no action will be taken. If the study is recruiting between 50% and 80% (between 22–33 and 44–69 for 12 and 24 months, respectively) of the intended rate, the ISDMC may recommend continuation only if strategies will be put in place to increase recruitment. If the study is recruiting at less than 50% (less than 22 and 44 for 12 and 24 months, respectively) of the intended rate, the ISDMC may recommend early termination of the study on the grounds of feasibility.

### Adverse events

All adverse events that occur from the point of the patient’s written informed consent are to be reported, even if the patient has not started taking VPA. All adverse events should be reported up to the point of the primary endpoint being established, with the exception of malignant transformation or new head and neck cancer, which should be collected until trial closure. All non-serious adverse events (AE)/adverse reactions (AR), whether expected or not, will be recorded in the relevant page of the CRF. Serious adverse reactions (SARs), serious adverse events (SAEs) and suspected unexpected serious adverse reactions (SUSARs) should be reported within 24 h of the local site becoming aware of the event. The SAE form asks for the nature of event, date of onset, severity, corrective therapies given, outcome and causality. The responsible investigator should sign the causality of the event. Additional information should be sent within 5 days if the reaction has not resolved at the time of reporting. The LCTC will notify the MHRA and main Research Ethics Committee (REC) of all SUSARs occurring during the study according to the following timelines; fatal and life-threatening within 7 days of notification and non-life-threatening within 15 days. All investigators will be informed of all SUSARs occurring throughout the study. Local investigators should report any SUSARs and/or SAEs as required by their Local Research Ethics Committee and/or Research and Development Office.

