#### Arm A

VPA (Epilim) will initially be taken orally for 14 days at a dose of 500 mg once daily. From day 15 until 4 calendar months after day 1, VPA will be taken orally continuously at a dose of 500 mg twice daily. A 5-mm punch biopsy will be taken at the 4-month time point.

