#### Arm B

Patients in the control group will not receive any trial medication. They will be monitored at the same intervals as patients in Arm A (2, 4 and 6 months from baseline) and will subject to the same blood monitoring schedule. A 5-mm punch biopsy will be taken at the 4-month time point, as for Arm A.

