### Schedule of events

Figure 1 shows the flow of patients through the trial and the SPIRIT figure (Fig. 2) gives details of the procedures required at each trial time-point. A screening biopsy (incisional biopsy) is taken to confirm eligibility, prior to randomisation. Patients are randomised to one of two arms (sodium valproate or observation only), for 4 months. A repeat biopsy is taken on the final day of trial medication at the 4-month time-point for both groups. A clinical photograph and bloods are also taken at this visit for both groups. In total the patient is examined five times during the trial period for signs of lesion progression.

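### Adverse event reporting ends at an undated efficacy event, so capture of events after the month-4 biopsy, after surgery and after the last dose is neither assured nor equal between patients

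*Protocol article*

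**What the plan says.** The Adverse events section opens the window at consent: "All adverse events that occur from the point of the patient’s written informed consent are to be reported". It closes the window with "All adverse events should be reported up to the point of the primary endpoint being established". The one carve-out concerns cancer outcomes, which the section follows to the end of the trial. No separate collection window is given for serious events.

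The events around month 4 are set out elsewhere in the article:

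- **Arm A:** "From day 15 until 4 calendar months after day 1, VPA will be taken orally continuously". In the same section, "A 5-mm punch biopsy will be taken at the 4-month time point".
- **Schedule of events:** "A repeat biopsy is taken on the final day of trial medication at the 4-month time-point for both groups". The photograph and bloods are taken at the same visit.
- **Potential risks of delay to surgical treatment:** patients listed for excision "will have their surgery scheduled at the end of month 4 of the study".
- **Arm B:** controls are monitored at the same times as Arm A, namely "2, 4 and 6 months from baseline".
- **Total responsiveness score:** the primary endpoint is the sum of size, histology and LOH response scores. Confirmed transformation is classed as progression whatever the score.
- **Schedule of events (text under Fig. 2):** an adverse event questionnaire is used at three points and at unscheduled visits. Blood counts, clotting and liver tests are done to look for drug toxicity.

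**The concern.** A safety window is normally closed by the calendar or by time since last dose. Here it is closed by an efficacy event whose date is never stated. The samples for that event are taken on the day dosing stops, so the rule provides no explicit follow-up after the last dose.

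That period matters in this trial. The article treats clotting and blood counts as a drug concern and lists thrombocytopenia among common effects. Tissue is cut on the last day of drug, and some patients go on to excision shortly afterwards. A bleed follows the cut, so it comes after the biopsy itself.

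Toxicity is named among the key secondary objectives, is a ground on which the ISDMC may make recommendations, and is meant to inform the phase III decision. If reporting stops at different times for different patients, toxicity counts rest on unequal observation. Events not collected at the time cannot be reliably recovered later.

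**Working it through.** The plan gives no figure to reproduce. The check sets the timeline against the cut-off under each possible meaning of *established*.

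**Inputs**

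| Event | Timing | Section |
|---|---|---|
| AE reporting starts | consent | Adverse events |
| Last dose (Arm A) | 4 calendar months after day 1 | Arm A |
| Endpoint biopsy, photograph, bloods | final dosing day, month 4 | Schedule of events |
| Listed surgery | end of month 4 | Potential risks of delay to surgical treatment |
| Last scheduled monitoring | month 6, both arms | Arm B |
| AE reporting ends | primary endpoint established; no date | Adverse events |

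**Reading 1: established means the month-4 assessment is done.** The cut-off coincides with the last dose.

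- Time after last dose with assured reporting: month 4 − month 4 = 0.
- Scheduled time left without it: month 6 − month 4 = 2 months.
- Share of the schedule covered, taking baseline as day 1: 4/6 = 67%.

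Bleeding after the biopsy, events after surgery and late reactions all fall beyond the cut-off.

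**Reading 2: established means all three components have been scored.** Histology and LOH need laboratory work on the month-4 tissue, and the Blinding section gives all three components to blinded assessors. The cut-off then falls at some date t after month 4, different for each patient and governed by turnaround. No turnaround time is given, so t cannot be computed. Some early post-biopsy events would be captured. Whether post-surgical or later events are captured depends on how fast a given sample was read.

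**Reading 3: confirmed transformation before month 4.** Total responsiveness score fixes these patients as progression automatically, and Clinical progression during the trial withdraws them. Their endpoint is arguably established at that moment, so reporting of other events may stop before month 4. If transformation differed by arm, so would the length of AE follow-up.

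**Can the loss be sized?** Sodium valproate safety profile puts common events, thrombocytopenia among them, at 1 to 10%. Applied to the 73 patients planned for the treatment arm: 73 × 0.01 = 0.7 and 73 × 0.10 = 7.3. This is not a count of missed bleeds. The band is a general frequency for the drug, not a prevalence at month 4. The document gives no bleeding rate, and the number of patients listed for excision is unknown. No estimate of missed events follows from it.

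**The case against.** The strongest reply is that the article never says reporting stops on the last dosing day. It dates the biopsy, not the endpoint. Histology and LOH scores cannot be complete that day, so on the literal wording the window runs past the last dose and may well catch an early bleed. This stands. A reader might infer a zero-day post-dose window as fact, but it is one reading of two.

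Second, the three questionnaire points are in a figure that is not shown. They may be months 2, 4 and 6, in which case month 6 already carries an AE form. A bleed that leads to an unscheduled trial visit would also meet the questionnaire. This stands too. But a month-6 questionnaire would then sit beyond the stated cut-off on Reading 1, and possibly on Reading 2, so the sections would still need reconciling.

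Third, the main exposure period is covered. Reporting runs from consent through dosing in both arms, and patients who stop the drug early remain under follow-up (Criteria for discontinuing or modifying allocated interventions). Thrombocytopenia found in the month-4 bloods is found at the endpoint visit itself. All true, but none of it moves the cut-off.

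Fourth, investigators are to be told of SUSARs arising at any time in the study. That is a duty to notify. It does not extend routine collection of ordinary AEs or SAEs.

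Fifth, the article never states that transformation establishes the endpoint; withdrawal may be what ends reporting. Reading 3 is therefore only a possibility.

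Finally, this is a condensed article, and the full protocol may define the term. The cut-off is nevertheless a rule that the article states, not a detail that it omits.

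**Conclusion.** The point holds as a badly fixed rule. The end of AE reporting is tied to an undated efficacy event. Followed as written, the window closes either at about the last dose (67% of the scheduled six months, with the last two not assured) or on a patient-specific date set by the laboratory. On neither reading is capture of post-biopsy, post-surgical and late drug events both assured and equal across patients.

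A reader might go further and conclude that such events definitely fall outside the data, that toxicity will be understated, or that 1 to 7 bleeds would be missed. The document supports none of these. It leaves *established* undated, leaves room for a month-6 questionnaire, and gives no rate of bleeding at month 4. The supportable statement is that toxicity may be understated, by an unknown amount.

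The conclusion rests on the article's wording of the cut-off and on there being no other AE or SAE window in the text shown. It should be corrected, because the loss could not be repaired reliably after the event and the correction is cheap.

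**What to change.** In the Adverse events section, replace the endpoint-linked cut-off with a fixed calendar end for AE and SAE collection: from consent to the existing month-6 visit, the same in both arms and whatever the endpoint status, including after confirmed transformation unless consent to follow-up is withdrawn. Keep the exception that follows malignant transformation and new head and neck cancer to trial closure.

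Reconcile this with the three questionnaire points in Schedule of events, stating which visits they are, and with the timing of the biopsy, surgery and month-6 visit. Tabulate on-treatment and post-treatment events separately, so that post-operative events do not blur the on-drug comparison.

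The cost is a change of wording and at most one more AE form at a visit already scheduled. The downside is that some post-operative events unrelated to the drug will be recorded; the separate tabulation keeps them visible as such.
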